## Abstract

**Aim:**

Statins have been shown to improve the possibility of a pathological complete response (pCR) in patients with locally advanced rectal cancer when given in combination with neo-adjuvant chemo-radiation (NACTRT) in observational studies. The primary objective of this phase II randomized controlled trial (RCT) is to determine the impact of rosuvastatin in improving pCR rates in patients with locally advanced rectal cancer who are undergoing NACTRT. The secondary objectives are to compare adverse events, postoperative morbidity and mortality, disease-free survival (DFS), and overall survival in the two arms and to identify potential prognostic and predictive factors determining outcomes. If the study is positive, we plan to proceed to a phase III RCT with 3-year DFS as the primary endpoint.

**Methods:**

This is a prospective, randomized, open-label phase II/III study. The phase II study has a sample size of 316 patients (158 in each arm) to be accrued over 3 years to have 288 evaluable patients. The standard arm will receive NACTRT while the intervention group will receive 20 mg rosuvastatin orally once daily along with NACTRT for 6 weeks followed by rosuvastatin alone for 6–10 weeks until surgery. All patients will be reviewed after repeat imaging by a multidisciplinary tumor board at 12–16 weeks after starting NACTRT and operable patients will be planned for surgery. The pathological response rate, tumor regression grade (TRG), and post-surgical complications will be recorded.

**Conclusion:**

The addition of rosuvastatin to NACTRT may improve the oncological outcomes by increasing the likelihood of pCR in patients with locally advanced rectal cancer undergoing NACTRT. This would be a low-cost, low-risk intervention that could potentially lead to the refinement of strategies, such as “watch and wait”, in a select subgroup of patients.

**Clinical trial registration:**

Clinical Trials Registry of India, identifier CTRI/2018/11/016459.

## Introduction

1

### Background

1.1

Colorectal cancer (CRC) is the third most common cancer in men (746,000 cases, 10.0% of the total) and the second in women (614,000 cases, 9.2% of the total) worldwide (1). In India, CRC is the third most common cancer (1, 2). In India, the annual incidence rates (AARs) for colon cancer and rectal cancer in men are 4.4 and 4.1 per 100,000, respectively (3).

The standard treatment for locally advanced rectal cancer (stage T3 and above and N1 and above) is neo-adjuvant chemo-radiation (NACTRT) followed by surgery and adjuvant chemotherapy (4, 5). The response to NACTRT is assessed by radiology and histopathology (4, 5). A pathological assessment is considered the gold standard tool for assessment of response (6). The prevalence of a pathological complete response (pCR)—defined as no residual cancer found on histological examination of the total mesorectal excision (TME) specimen—varies from 15%–27% following NACTRT (7). In addition to a favorable prognosis, if a complete response is noted at reassessment, a pCR permits a potentially rectal-preserving watch-and-wait strategy. Recent studies indicate a higher chance for a wait-and-watch strategy given the nearly double pCR rates previously reported in the UNICANCER-PRODIGE 23 (28% vs. 12%), RAPIDO (28% vs 14%), and STELLAR trials (22% vs 12%) (45). The patients who achieve pCR after NACTRT have better long-term outcomes, less propensity to develop local and distant recurrence, and improved survival (8). In these patients, sphincter-preserving procedures or organ-preserving options, such as local excision of residual tumor (9) or omission of surgery altogether, have been evaluated (10–12). In a meta-analysis including 3,105 patients, Maas et al. demonstrated (i) that the 5-year crude disease-free survival (DFS) rate of 484 patients who achieved a pCR after NACTRT was 83%, compared with 66% for those who did not have a pCR (*p* < 0.0001) and (ii) that the 5-year distal metastasis-free survival rate was 89% in the pCR group and 75% in the non-pCR group (*p* < 0.0001) (13). Further, patients with a pCR in the RAPIDO trial were divided into two groups: experimental [EXP,120/423, short-course radiotherapy, chemotherapy, surgery, and total neoadjuvant therapy (TNT)] and standard-of-care treatment (STD, 57/398, CRT, surgery, postoperative chemotherapy depending on hospital policy). They reported the 5-year overall survival (OS) rate was 94% [95% confidence interval (95%CI)= 90–98] in the EXP group and 93% (95%CI= 87–100) in the STD group [hazard ratio (HR) =1.41, 95%CI =0.51–3.92; p = 0.50] (45).

Achieving a pCR following NACTRT is probably a prerequisite for improved outcomes in rectal cancer (7) using neo-adjuvant therapy. There have been multiple strategies suggested to improve pCR with mixed results including induction chemotherapy prior to and after NACTRT, delay in surgery after NACTRT, chemotherapy, and short-course radiotherapy. Recent total neoadjuvant (TN) trials have shown improved complete response rates using a combination of induction or consolidation chemotherapy with either long-course or short-course radiotherapy (14–17). A meta-analysis study for locally advanced rectal cancer was conducted to compare the efficacy of TN and NACTRT (38). The analysis considered six studies with 12,812 subjects for the meta-analysis and reported no significant difference in pCR and local relapse rate. Furthermore, distant metastasis was found to be better with TN than with NACTRT (14.3% vs. 20.4%), while the difference was not statistically significant [Odds ratio (OR)=0.84, 95%CI =0.31–2.27] (38). None of these trials were without toxicity related to treatment intensification. The addition of contact brachytherapy to NACTRT also increases complete response in small-sized tumors (18). If an increase in pCR rates can be achieved without increasing the treatment duration or adding toxicity, it would be worth exploring. One strategy that might improve the pCR is to add statins due to their anti-neoplastic effect along with NACTRT even though it is not an established strategy (19, 20). Few observational studies have suggested the benefit of statins in rectal cancer (19, 20) in terms of pCR, but pCR has been incidentally noted following NACTRT in patients receiving statins. The pCR rate was 25%–30% with statins compared to 15%–17% without statins (19, 20). In a phase II trial study wherein simvastatin was added along with chemoradiotherapy (CRT) and capecitabine in patients with locally advanced rectal cancer, the pCR rate was 18.9% (n=10) in the per-protocol analysis (46). Further, in an observational study, the authors reported that the disease-free survival did not vary (HR=0.98, CI=0.77–1.25, p=0.88) even if the patients were given statins along with CRT (47). However, there are no completed randomized controlled trials (RCTs) on the third-generation statin, rosuvastatin, in patients with locally advanced rectal cancer. Furthermore, an increasing amount of data suggests that obesity, dietary variables, and lipids directly contribute to the development of various cancerous tumors, which frequently result in treatment resistance and metastasis (44). Therefore, aggressive malignant tumors may become more vulnerable if statins are used as an adjuvant in anti-neoplastic treatment regimens. Mechanistically speaking, apoptosis, the suppression of proliferation via STAT3/SKP2 signaling, and the modification of the YAP/CD44 growth axis through YAP inactivation are the significant mechanisms behind statins’ anti-neoplastic effects (44). By downregulating TAZ, which is mediated by p53 transcriptional overexpression, statins have been demonstrated to impact the viability of cancer cells (44). According to a recent study, statins may cause epigenetic changes by inhibiting DNA methyltransferases (DNMT) while supporting CRC stem cell differentiation (44). These novel attributes of statins, however, which include focusing on the inhibition or degradation of carcinogenic proteins, offer novel perspectives of how statins work, whether they work in tandem with or independently of the cholesterol pathway.

The mechanisms of action of statins are manifold. Inhibition of hydroxymethylglutaryl- CoA (HMG-CoA) reductase by statins leads not only to a decrease in circulating low-density lipoprotein (LDL) cholesterol, but also to reduced production of other intermediates of the mevalonate pathway, including the non-sterol isoprenoids, farnesyl, pyrophosphate, and geranylgeranyl pyrophosphate (21). Farnesyl pyrophosphate and geranylgeranyl pyrophosphate are required for post-translational modification (iso-prenylation) and biological activity of a wide variety of cellular proteins, including the small guanosine triphosphatases Ras and Rho (22), which are strongly implicated in carcinogenesis (23, 24). Modulation of iso-prenylation appears to be a central mechanism through which statins exert their anti-proliferative and pro-apoptotic effects (23–25). Statins are known to exert a variety of effects, including having anti-cancer properties, in addition to their ability to lower cholesterol levels (43). Hence, repurposing statins in cancer therapeutics could be crucial for increasing the overall survival of patients (44). Dysregulation of the mevalonate pathway may be implicated in neoplastic transformation and tumor progression and this may partly explain the tumor-selective effects of statins (26, 27). A number of HMG-CoA reductase-independent mechanisms have also been proposed to account for the pleiotropic effects of statins, including antioxidant activity (28) and effects on cell adhesion (29, 30), inflammation (31, 32), immune regulation (33), and angiogenesis (34).

The type and dosage of statins have varied in retrospective observational studies (19, 20). Chemoprevention studies have used first- and second-generation statins more commonly and the mean dosage has been 30–40mg (35). The mean dosage was 30–40 mg when given along with NACTRT (20). Rosuvastatin is a third-generation statin with very minimal toxicity (36). Given its structural difference and hydrophilic nature, it provides better efficacy compared to other statins (42). The standard dose of rosuvastatin is 5-40mg. The 40mg dose is used only when the serum LDL goal is not reached by standard dosage, however, it can be associated with an increased risk of adverse events, especially in some subgroups such as Asian patients and women (37). Therefore, we proposed using a mean rosuvastatin dosage of 20 mg in the trial to have minimal side effects as we are using rosuvastatin as an adjunct to the chemotherapy.

Furthermore, to understand the molecular mechanism, it is crucial to investigate the effect of statins on the chromatin organizer Special AT-rich binding protein 1 (SATB1), a downstream target and master regulator of Wnt signaling (44, 49). It has been shown that SATB1 directly affects the onset and spread of various cancers such as colorectal (50) and breast cancer (51). Further, statins treatment is known to downregulate SATB1 in colorectal cancer cells (52) but the effect on its homolog SATB2 is not known. Therefore, examining the expression level of SATB proteins following statins administration along with NACTRT versus NACTRT alone would provide a comprehensive understanding of the probable molecular mechanism of action for the therapeutic effectiveness of rosuvastatin.

### Study rationale

1.2

A pCR following NACTRT has been associated with decreased local recurrence and improved recurrence-free survival in rectal cancer. Statins have been shown to induce better pCR in combination with NACTRT in observational studies (39). This study aims to assess whether this observation is true through the conduct of a randomized study comparing treatment with statins along with NACTRT versus NACTRT alone (**Table 1A**).

**Table 1A T1:** Summarized study hypothesis and objectives.

	Phase II	Phase III
Hypothesis	The addition of Rosuvastatin to NACRT will improve the pathological complete response rate by 10% (from 15% to 25%)	The addition of Rosuvastatin to NACTRT will improve the 3-year disease-free survival by 7% (from 60% to 67%)
Primary objective	To determine the impact of rosuvastatin in improving the pCR rate in patients with localized rectal cancer undergoing neoadjuvant chemoradiotherapy	To determine the impact of rosuvastatin in improving 3-year DFS in patients with localized rectal cancer undergoing neoadjuvant chemoradiotherapy
Secondary objectives	•The frequency and severity of adverse events in the two arms as assessed by CTCAE v4.03 •To compare postoperative morbidity and mortality in the two arms •To identify other potential prognostic and predictive factors determining outcomes •To compare the disease-/progression-free survival in the two arms •To compare the overall survival in the two arms	•To compare the 5-year overall survival in the two arms •To compare the adverse events in the two arms •To identify other potential prognostic and predictive factors determining outcomes •To compare the patterns of recurrence in the two arms

The molecular sub-study aimed to study the combined expression patterns of SATB family chromatin organizers which would provide a better understanding of colorectal cancer disease progression and would establish them as an unequivocal prognostic marker and a potential therapeutic marker for statins therapy (**Table 1B**, **Figure 1**). The complete details of the molecular sub-study is mentioned in **Appendix 5** in **Supplementary Material**.

**Table 1B T2:** Objectives for molecular sub-study.

Rationale	The molecular sub-study aims to study the combined expression patterns of SATB family chromatin organizers which would provide a better understanding of CRC disease progression and would establish them as an unequivocal prognostic marker and a potential therapeutic marker for statin therapy.
Objectives	•Evaluate expression and localization of SATB1 and SATB2 across paired human colon/rectum and tumor samples •Correlation of expression of SATB1 and SATB2 across different grades and stages of tumor samples towards understanding CRC progression •Understand the role of SATB proteins in tumor regeneration and disease relapse by validation of the association of its expression across differentiated and undifferentiated tumors •Correlation of expression of SATB proteins across colorectal cancer subtypes-Classical adenocarcinoma, mucinous adenocarcinoma, and signet ring pathology tumors

**Figure 1 f1:**
[figure not shown]
Flow chart depicting the molecular sub-study.

### Study hypothesis and objective(s) in the phase II part

1.3

Hypothesis:

The addition of rosuvastatin to NACTRT will improve the pCR rate by 10% (from 15% to 25%).

Primary objective:

To determine the impact of rosuvastatin in improving pCR in patients with locally advanced rectal cancer undergoing NACTRT.

Secondary objectives:

To compare the frequency and severity of adverse events in the two arms.To compare post-operative morbidity and mortality in the two arms.To identify other potential prognostic and predictive factors determining outcomes.To compare the DFS in the two arms.To compare the OS in the two arms.Evaluate expression and localization of SATB1 and SATB2 across paired human colon/rectum and tumor samples.Correlation of expression of SATB1 and SATB2 across different grades and stages of tumor samples towards understanding CRC progression.Understand the role of SATB proteins in tumor regeneration and disease relapse by validation of the association of its expression across differentiated and undifferentiated tumors.Correlation of expression of SATB proteins across colorectal cancer subtypes-classical adenocarcinoma, mucinous adenocarcinoma, and signet ring pathology tumors.

If the phase 2 study has positive results, we plan to proceed to a phase 3 study.

### Study hypothesis and objective(s) in the phase III part

1.4

Hypothesis:

The addition of rosuvastatin to NACTRT will improve the 3-year DFS by 7% (from 60% to 67%).

Primary Objective:

To determine the impact of rosuvastatin in improving 3-year DFS in patients with locally advanced rectal cancer undergoing NACTRT.

Secondary objectives:

To compare the 5-year OS in the two arms.To compare the adverse events in the two arms.To identify other potential prognostic and predictive factors determining outcomes.To compare the patterns of recurrence in the two arms.

## Methods

2

### Study design

2.1

The study is a prospective, randomized, open-label phase II/III study.

For the phase II part of the study, eligible patients will be randomized 1:1 to the statin + NACTRT arm or the only NACTRT (standard) arm. The statin arm will receive rosuvastatin 20 mg for 12–16 weeks. Pathological response would be assessed following surgery.

A follow-on phase III trial with 3-year DFS as the endpoint will be planned depending on how the statin arm fares in terms of feasibility, safety, and efficacy.

### Inclusion and exclusion criteria

2.2

### Detailed methodology

2.3

#### Screening

2.3.1

All patients diagnosed as having rectal cancer will undergo a standard staging workup that includes but may not be limited to a colonoscopy, biopsy, pelvis MRI, and contrast-enhanced computed tomography (CECT) of the thorax and abdomen, carcino embryonic antigen (CEA), complete blood count and biochemistry tests [random blood sugar (RBS), liver function test (LFT), and renal function test (RFT)]. This is part of the standard care. Treatment decisions are taken by a multi-disciplinary tumor board (MDTB). Previously untreated rectal cancer patients who are planned for NACTRT will be screened for the study and an anonymized screening log will be maintained.

#### Enrolment in the study/consent

2.3.2

All patients eligible for study participation who satisfy the inclusion/exclusion criteria (**Table 2**, **Appendix 4** in **Supplementary Material**) will be enrolled after an informed consent form (ICF), provided by a study team member, is signed. An enrolment log will be maintained and a study ID will be allocated to each patient at study entry.

**Table 2 T3:** Inclusion and exclusion criteria.

Inclusion criteria	Exclusion criteria
•Age between 18–70 years •Subjects willing to sign the informed consent •Eastern Cooperative Oncology Group (ECOG) performance status 0 to 2 •Histologic diagnosis of rectal adenocarcinoma •Clinical and radiological T2–4 (any) N (any) M0 •Fit to receive neoadjuvant chemoradiotherapy •Absence of colorectal synchronous primary •No prior rectal cancer treatment received	•Patients with proven metastatic disease •History of Crohn's disease or ulcerative colitis •Inherited polyposis syndromes •Ongoing statin or aspirin therapy for cardiovascular disease •Pregnant or nursing women •Subject not willing to provide informed consent •Comorbidities precluding statins and neo-adjuvant therapy including but not limited to Hepatitis **, *acute or chronic kidney disease* •Prior anti-neoplastic therapy •Patients already taking the following drugs: cyclosporine, gemfibrozil, atazanavir/ritonavir, lopinavir/ritonavir, tipranavir/ritonavir or simeprevir, eltrombopag, dronedarone, itraconazole, fluconazole or ketoconazole; coumarin anticoagulants; lipid-lowering therapies: fibrates or lipid-modifying doses (greater than or equal to 1g/day) of niacin; aluminum and magnesium hydroxide combination; antacid; and erythromycin. *Hepatitis will be defined as sustained elevation of transaminases (two readings 5–7 days apart) ≥3X upper limit of normal. *Kidney disease will be defined as elevated creatinine levels above the upper limit of normal

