##### Study intervention

2.3.4.2

Patients in the study arm will receive 20 mg rosuvastatin orally once daily along with NACTRT for 6 weeks followed by rosuvastatin alone for another 6–10 weeks until surgery (12–16 weeks of statin therapy until surgery or confirmation of ineligibility for surgery). Patients in the control arm will receive only NACTRT as described above, which is the standard of care (**Figure 2**).

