### Sample size and duration of the study

2.4

Each year, approximately 180–200 rectal cancer patients receive NACTRT at our hospital, with approximately 70% undergoing surgery and 15%–20% developing progressive disease. The current pCR rate at our hospital following NACTRT is approximately 15%, while the literature indicates a pCR rate of 25%–30% with statin therapy. We hypothesize that rosuvastatin can increase the pCR rate by 10%, from 15% to 25%. To detect a 10% difference in pCR rates, with a two-sided alpha of 0.10 and 80% power, a sample size of 288 patients would be required. Factoring in a 10% attrition rate, the total sample size increases to 316. Approximately 500–600 patients will need to be screened to enroll 316 participants. It is estimated that accrual and analysis will take approximately 3 years to complete.

A follow-on phase III trial is also will be planned depending on the success of the phase II study, which will compare the 3-year DFS in the two arms. All the patients in the phase II study will be included in the survival statistics in the follow-on phase III study which will be statistically powered for survival. Assuming that the addition of rosuvastatin to NACTRT will improve the 3-year DFS from 60% to 67%, our calculated sample size will be 1,135 subjects (567 in the control group and 568 in the treatment group) (a two-sided log-rank test with 80.0% power at a 0.050 significance level). This assumes a uniform accrual pattern across time periods and 10% dropout rate. If we move on to the phase III study, another 4 years will be required for accrual. The total duration will be 7 years for accrual and 3 years for follow up.

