### Rosuvastatin administration

3.2

A member of the study team will prescribe the drug and give instructions about its usage. Regular intake of the drug will be confirmed by weekly telephonic calls with the study coordinator. Patients will be followed up at regular intervals according to the study protocol unless any adverse events occur, which will be managed immediately. Drug compliance will be monitored and noted in the CRF.

The details of rosuvastatin drug toxicity, dose modification, possible drug interactions, concomitant therapy in the study, and dosing delays/dose modifications are mentioned in **Appendix 3** in **Supplementary Material**.

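### Table 2 bars ongoing statin use only when it is for cardiovascular disease, so its wording may admit other statin users to a trial of statin versus no statin

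*Protocol article*

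**What the plan says.** Four places in the protocol article bear on this.

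- **Table 2 (section 2.3.2), statin item.** The exclusion reads "Ongoing statin or aspirin therapy for cardiovascular disease".
- **Table 2, other items that touch statins or lipid drugs.** One excludes "Comorbidities precluding statins and neo-adjuvant therapy". The list of excluded drugs has an entry for "lipid-lowering therapies: fibrates or lipid-modifying doses (greater than or equal to 1g/day) of niacin". Statins are not in that list.
- **Section 2.3.4.2.** "Patients in the control arm will receive only NACTRT as described above, which is the standard of care".
- **Section 1.1.** The rationale draws on observational work in which "pCR has been incidentally noted following NACTRT in patients receiving statins". Rates of 25%–30% with statins are set against 15%–17% without.

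Section 2.3.2 also cites Appendix 4 for the eligibility criteria. Section 3.2 says that possible drug interactions, "concomitant therapy in the study, and dosing delays/dose modifications are mentioned in" Appendix 3. Neither appendix was available for this review.

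**The concern.** The trial tests whether a statin raises the pCR rate, so the criterion that matters most for the contrast is the one that keeps statins out of the control arm. That criterion is limited by indication. A patient without cardiovascular disease who takes a statin for raised cholesterol or diabetes does not meet it as written.

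The article gives no scientific reason for the limit. Its own rationale comes from patients who happened to be on statins, and section 1.1 notes that statin type and dosage varied in those studies. On that reasoning a background statin could act on pCR whatever it was prescribed for.

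If such patients are randomised and stay on their statin, those in the control arm are exposed to the tested drug class. The observed difference then shrinks towards zero, and the comparison is no longer cleanly statin versus no statin. It would also be hard to square with controls receiving chemoradiation only.

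**Working it through.** **Does another criterion close the gap?** Take a patient on a statin for dyslipidaemia, without cardiovascular disease, and go through Table 2.

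- *Statin or aspirin item:* not met, because the indication is not cardiovascular disease.
- *Comorbidity item:* concerns patients whose conditions rule out statins, not patients already taking one.
- *Excluded-drug list:* its lipid-lowering entry covers fibrates and niacin at 1 g/day or more.
- *Prior anti-neoplastic therapy:* a statin taken for lipids is not that.

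No criterion printed in the article excludes this patient.

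**Inputs for the size (section 2.4).** pCR 15% versus 25%, 80% power, two-sided alpha 0.10, 288 evaluable. Allocation is 1:1 (section 2.3.3), so 144 per arm.

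**The plan's own figure first.** With pooled variance under the null, mean rate 0.20:

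n per arm = [z_α √(2 × 0.20 × 0.80) + z_β √(0.15 × 0.85 + 0.25 × 0.75)]² / 0.10²

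- One-sided 0.10 (z_α = 1.2816, z_β = 0.8416): (0.7250 + 0.4723)² / 0.01 = 143.4, so 144 per arm and 288 in total. This matches.
- Two-sided 0.10 as stated (z_α = 1.6449): (0.9305 + 0.4723)² / 0.01 = 196.8, so 197 per arm and 394 in total. This does not match.

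That mismatch is a separate matter. Here it only means that power has to be shown at both levels.

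**Dilution.** Let f be the share of controls on a background statin. The article does not give it, so the values of f below are assumptions. Two further assumptions: a background statin has the full 10-point effect, and the study arm stays at 25%.

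Control rate p_c = 0.15 + 0.10 f; difference d = 0.25 − p_c; p̄ = (p_c + 0.25)/2.

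Power = Φ{ [d √144 − z_α √(2 p̄(1 − p̄))] / √(p_c(1 − p_c) + 0.25 × 0.75) }

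For f = 10%, one-sided: p_c = 0.16, d = 0.09, p̄ = 0.205, giving (1.08 − 0.7317)/0.5674 = 0.614 and Φ = 73.0%.

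| f | Control pCR | Difference (points) | Power, one-sided 0.10 | Power, two-sided 0.10 |
|---|---|---|---|---|
| 0 | 15.0% | 10.0 | 80.1% | 68.4% |
| 2% | 15.2% | 9.8 | 78.8% | 66.8% |
| 5% | 15.5% | 9.5 | 76.7% | 64.2% |
| 10% | 16.0% | 9.0 | 73.0% | 59.8% |

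**Sensitivity to the assumed effect.** Only the product of share and effect enters the control rate. If 10% of controls took a statin with a 5-point effect, the control rate would be 0.15 + 0.05 × 0.10 = 15.5%, which is the 5% row. A smaller background effect means a smaller loss.

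**The case against.** A reader might infer that these patients are definitely eligible, and that they do contaminate the control arm or take two statins in the study arm. The article does not support that.

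- **The wording has other readings.** The indication may attach to aspirin only, or may be meant loosely enough to include prevention. This stands as an argument about intent. It does not rescue the wording: a rule on the tested drug class that site staff can read in several ways should be made plain.
- **Appendices 3 and 4 may settle it.** They could bar all statins or say how a background statin is handled. This stands, and it limits the point to what Table 2 says. If an appendix does bar all statins, Table 2 states the rule too narrowly and needs correcting; if not, the gap is open.
- **The rest of the article points to a control arm without statins.** Section 2.3.4.2 says so, and section 2.6 speaks of statin and non-statin groups. That makes a gap in drafting more likely than a deliberate allowance, but it excludes nobody.
- **The size is unknown.** Patients are at most 70 years old, and those on statins for cardiovascular disease are already out, so the remaining share may be small. Giving every background statin the full 10-point effect is generous: section 1.1 itself reports a pCR rate of 18.9% when simvastatin was added to chemoradiotherapy. Both points stand.

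It is also tempting to ask for a statin-free period before entry and for a wider aspirin exclusion. The article claims no aspirin effect on pCR and gives no ground for either, so neither is part of this point.

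**Conclusion.** The point holds as a defect in a stated rule. Table 2 limits the statin exclusion by indication, nothing else printed in the article covers the remaining statin users, and this sits badly with a control arm that receives chemoradiation only. Contamination is possible, not established: it requires such patients to enrol, their statin to continue, and no rule in Appendices 3 or 4 to prevent it.

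Dilution of the contrast would be towards no difference. For 2% to 10% of controls affected, the loss is about 1 to 7 points of power at one-sided 0.10 and about 2 to 9 points at the stated two-sided 0.10. These figures rest on an assumed share and on the full hypothesised effect for any background statin; a smaller share or effect makes them smaller. The change is worth making because it protects the main contrast at almost no cost.

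**What to change.** Reword the Table 2 exclusion to cover any ongoing statin use, regardless of indication, and reconcile Table 2 with Appendices 3 and 4 so that all three state the same rule.

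For patients already enrolled, check whether baseline statin use was recorded. The article mentions case record form entries for pill counts and compliance but describes no baseline medication record, so this cannot be taken for granted. If it was recorded, add a sensitivity analysis of pCR that leaves out baseline statin users in both arms. Baseline use is fixed before randomisation, so the comparison among the remaining patients is still randomised.

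The cost is a one-line amendment, the appendix check and a few more screen failures. No extra tests are needed, and the sample size calculation does not change on this account.
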